## Abstract

**Background:**

Despite active national initiatives, the low prevalence of modern contraception in Pakistan remains unchanged, leading to high rates of unintended pregnancies and poor maternal and neonatal outcomes. Conventional directive counseling does not sufficiently cater to women’s needs, whereas structured client-centered strategies like GATHER (greet, ask, tell, help, explain, return) and the balanced counseling strategy (BCS) may improve outcomes. Existing literature assessing the comparative effectiveness of these strategies in the Pakistani population lacks evidence.

**Objective:**

The study aim is to compare the effectiveness of routine counseling, GATHER, and the BCS in improving client satisfaction with, and uptake of, modern contraceptives.

**Methods:**

This is a pilot, 3-arm, single-blinded, parallel, cluster-randomized trial conducted in tertiary care hospital–affiliated family health centers in Rawalpindi, Pakistan. It is a 3-phased trial, first assessing baseline data on contraceptive uptake and discontinuation determinants among 333 women of reproductive age. The second phase will provide structured training to service providers based on either GATHER or the BCS in each arm. After training, assessments will be performed at 3- and 6-month intervals to evaluate contraceptive uptake and counseling quality improvements. In the last phase, a qualitative analysis will be done through focus group discussions and in-depth interviews to identify barriers to implementation and to assess scalability. Analyses will be done using SPSS (version 26; IBM Corp). Analyses of quantitative and qualitative data will be done using mixed effects models and thematic analysis, accounting for clustering, to evaluate the interventions’ effects on contraceptive uptake and client satisfaction.

**Results:**

Delivery of the intervention is underway, and baseline data from the 333 participants have been collected. The first follow-up assessments are planned at intervals of 3 and 6 months. However, no outcome data have been obtained or analyses performed at this stage.

**Conclusions:**

This pilot trial is expected to generate evidence on the effectiveness of structured, client-centered counseling strategies in comparison to conventional routine practices, showing improved uptake of contraceptive use and satisfaction in Pakistan. The findings are expected to facilitate the design of comprehensive and scaled-up trials and guide national family planning programs and the integration of rights-based counseling strategies.

## Introduction

In low- and middle-income countries, a lack of access to contraception affects millions of women, causing unintended pregnancies and poor maternal and child health. To reduce risks, including preterm birth and stunting, the World Health Organization (WHO) recommends a 24-month interval between births. Despite this recommendation, short intervals and high fertility rates continue to stand as major health concerns [1,2]. The United Nations Sustainable Development Goals include improving contraceptive access and maternal care, which are essential for reducing the global maternal mortality ratio to less than 70 maternal deaths per 100,000 live births by 2030. Despite major investments in this field, the unmet need for modern contraception is significant, and many maternal- and neonatal-related complications are preventable. Sustainable Development Goals 3.7 and 5.6 emphasize universal access to reproductive health and gender equity, but progress toward these goals remains deficient. Despite the improvement in contraceptive availability, other services, including counseling, remain insufficient for improving the actual uptake of contraception. It is now important to shift the approach toward a well-structured, client-centered one and away from a conventional directive strategy, so as to improve the ability of women to make informed choices, increase their autonomy, and ensure reproductive justice [3,4].

Pakistan’s health care system remains dependent on out-of-pocket payments, with almost 75% of the population relying on private health services. This situation exacerbates existing inequities and restricts access to essential reproductive health care for the most vulnerable groups. In high-income nations, robust public health infrastructure and universal coverage have led to increased life expectancy, and even countries with limited resources, such as Brazil and Ethiopia, have achieved notable improvements in health outcomes through focused public investment and health system reforms. Pakistan, however, continues to experience inconsistent and fragile progress in family planning (FP) [5,6]. Pakistan’s contraceptive prevalence rate has shown modest growth, from 29.6% in 2007 to 35.5% in 2012, but has since stagnated at 34.3% (Pakistan Demographic and Health Survey 2017‐18 [7]), with the prevalence rate for modern methods of contraception plateauing at 25%. Deep provincial disparities persist, from 46% in Islamabad to just 20% in Baluchistan, underscoring inequities in access and service quality. Despite aligning with the Family Planning 2030 (FP2030) goals through the Council of Common Interest and a national action plan, systemic barriers such as shortages, workforce gaps, and poor integration with maternal health services continue to impede progress [8,9].

Factors such as insufficient educational attainment and limited decision-making authority have been recognized as obstacles to the adoption of contraceptive methods, underscoring the necessity for customized counseling strategies [10-12]. Comprehensive contraceptive counseling is vital for informed decision-making and sustained use of modern methods. Unfortunately, in Pakistan, counseling services are often inadequate. Counseling in family health centers (FHCs) is often directive rather than client-centered, leading to poor communication, lack of informed decision-making, poor client satisfaction, and limited contraceptive continuation [13]. Service providers are frequently overburdened and unable to allocate sufficient time for detailed counseling, and there is a lack of trained personnel to deliver culturally sensitive, accurate information [10]. It is imperative to enhance both the coverage and quality of counseling services, alongside addressing systemic and sociocultural barriers, to improve the efficacy of FP programs in Pakistan [14-16].

Ensuring access to diverse contraceptive methods and providing high-quality, noncoercive counseling are essential for effective FP [17]. Training programs for counseling should focus on both technical skills and reproductive rights, equipping service providers with up-to-date medical knowledge and the ability to offer a full range of contraceptive options [18,19]. GATHER (greet, ask, tell, help, explain, return) is the traditionally used counseling model in Pakistan’s public health system, while the balanced counseling strategy (BCS) is a newer, evidence-based approach introduced through recent donor-supported programs. The BCS offers a more structured, client-tailored process that may improve informed choice and efficiency. Comparing these two models will allow for evidence-based guidance on which one better enhances contraceptive uptake and satisfaction, supporting policy decisions under Pakistan’s FP2030 commitments [10].

## Methods

### Study Framework

The theory of change construct will be used in this study. Using this theory enables interventions to improve client satisfaction and service provider competency through training and measure these improvements in terms of behavioral change, thereby making FP services more effective. The current trial plans to assess the effectiveness of 3 counseling approaches in improving the uptake of modern contraceptives over a period of 6 months: sensitization, GATHER, and the BCS. The study hypothesis is that contraceptive uptake will differ among the 3 approaches.

The duration of the trial will be 8 to 9 months, structured in 3 phases. The first phase is a formative phase, during which baseline assessments will be obtained. This will be followed by the interventional phase, in which service providers will be given training specific to the study arm they are allocated to. The last phase will be an exploratory phase meant to identify enablers and barriers and other findings that can facilitate the scaling-up of the study. The conceptual framework of the study is shown schematically in Figure 1.

**Figure 1. F1:**
[figure not shown]
Conceptual framework of the study.

For this study, modern methods of contraception include birth control pills, female and male sterilization, intrauterine contraceptive devices, injectable contraceptives, implants, male condoms, and emergency contraception [20]. A client-centered approach is defined as one based on understanding a woman’s fertility goals and contraceptive needs and preferences, providing education on contraceptive methods and autonomy, and encouraging open dialogue [21].

The GATHER approach for FP is a structured counseling strategy. Service providers follow the 6 steps in the approach’s name (greet, ask, tell, help, explain, and return). This structured approach helps providers build rapport, explore the goals and concerns of the client, provide tailored contraceptive information, facilitate the informed decision-making ability of the client, comprehensively explain the use of contraceptives, and, lastly, schedule a return visit for follow up [22].

The BCS is also a structured, evidence-based strategy for FP counseling. It follows three steps: (1) the pre-choice step, in which the service provider assesses the client’s needs and provides tailored information; (2) the choice of method step, in which the client and provider discuss contraceptive options and address the concerns of the client; and (3) the post-choice step, in which the provider reinforces correct use of the chosen method and provides follow-up assistance. This strategy enables decision-making and contraceptive adherence in clients and improved client satisfaction.

Effective FP counseling improves knowledge, autonomy, and contraceptive use. Key factors include clear communication, client engagement, respect for choices, and follow-up support. Success is measured by satisfaction, continued use, reduced discontinuation, and alignment with reproductive goals [23].

### Study Aim

Broadly, this study aims to evaluate the effectiveness of 3 contraceptive counseling approaches in improving modern contraceptive uptake in FHCs across Rawalpindi, Pakistan: sensitization, GATHER, and the BCS. Specifically, the study will determine the impact of each counseling intervention on modern contraceptive uptake, client satisfaction, and service provider competence at 3 and 6 months after the intervention; conduct a cross-sectional baseline analysis to examine sociodemographic, cultural, and health system factors associated with contraceptive use and discontinuation; identify key barriers and facilitators to contraceptive uptake through integrated quantitative and qualitative methods; compare uptake trends and determinants of contraceptive adoption between intervention and control groups; and generate context-specific evidence to inform the integration of scalable, rights-based counseling models into Pakistan’s national FP programs.

### Study Design

This study is designed as a pilot, 3-arm, single-blinded, parallel, cluster-randomized pilot trial. It will evaluate the effectiveness of 3 counseling approaches (sensitization, as a control; GATHER; and the BCS) in improving modern contraceptive uptake. The trial will include both quantitative and qualitative components: a quantitative analysis to assess changes in contraceptive uptake, service provider competence, and client satisfaction; and a qualitative analysis to explore barriers, facilitators, and scalability. The unit of clustering is at the hospital catchment level, with FHCs nested within clusters considered as a single cluster and randomized to 1 of the 3 arms. The clustering at the hospital level is intended to minimize contamination across study arms. Clients enrolled in the trial will be blinded to the counseling strategy they receive.

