### Study Setting

A diverse population resides in Rawalpindi, with varying socioeconomic backgrounds and cultural identities, making it a suitable place to assess the effect of a client-centered counseling approach on FP uptake. The study trial is conducted at tertiary care hospitals and their affiliated FHCs. Rawalpindi has an extensive network of nearly 60 FHCs that are administratively affiliated with tertiary hospitals.

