### Sampling Methods and Sample Size Calculation

#### Consecutive Sampling of Clients

In this initial phase, all eligible clients visiting selected tertiary care hospital–affiliated FHCs will be enrolled through nonprobability consecutive sampling. The sample size for this phase was calculated using the WHO sample size calculator [24], with a margin of error of 0.05, 95% CIs, and assumed prevalence of modern contraceptive uptake of 27%, as reported for Punjab in the Pakistan Demographic and Health Survey 2017‐18. A sample size of 333 participants was calculated using these parameters.

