#### Stratified Random Sampling of Centers

Stratified random sampling of urban and rural locations was used in the second phase of the trial. FHCs affiliated with tertiary care hospitals were stratified by geographical location, followed by randomization through the lottery method into 3 study arms (one control arm and two interventional arms) to maintain objectivity and reduce selection bias.

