#### Study Participants: Purposive Sampling and Sample Size Calculation

For the final phase of the trial, women of reproductive age visiting FHCs for FP services will be recruited through purposive sampling to compare client satisfaction and uptake of modern contraceptive methods before and after the intervention. The sample size estimate considered feasibility and the ability to inform future scale-up studies covering larger populations.

Baseline modern contraceptive uptake in all arms was assumed to be approximately 25% based on estimates from the Pakistan Demographic and Health Survey 2017‐18. A collective review of systematic reviews and meta-analyses revealed that improved counseling strategies can increase contraceptive uptake up to 30% to 40%, corresponding to an absolute increase of nearly 8% to 18% in comparison to routine care [23]. Based on the above evidence, we assumed values of 25% and 40% for contraceptive uptake in the control and interventional arms, respectively. An absolute effect size of 15% or 0.15 points was assumed for this study.

The sample size was calculated using a standard formula for comparing 2 populations through testing the 1-sided hypothesis. The significance level was set at 5% (α=.05) for a power of 80% (1−β=0.80). Given the design of the study, a pragmatic approach was used. Consistent with values reported in health services literature, an intracluster correlation coefficient (ICC) of 0.02 [25] and design effect of 1.38 (DE=1+(m-1) x ICC) was applied. Following methodological guidance for pilot trials, the sample size was not inflated to meet confirmatory power requirements, and a sample size of 60 per arm and 180 across all 3 arms was chosen.

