##### Randomization and Blinding

Cluster randomization was conducted at the hospital level, with each hospital constituting a cluster. Hospitals with similar characteristics were grouped to maintain comparability, and randomization was performed using computer-generated methods, with stratification to balance key variables such as hospital size and patient demographics. This strategy helps in minimizing contamination and bias in allocation.

For the interventional phase, the interventional arms are implementing the standardized counseling approach for which they were trained, whereas the control arm continues routine practices. Clients will remain blinded to the counseling approach they are provided, but owing to the nature of the interventions, the service providers know which arm they are assigned to. Although this is a study design limitation, it is standard practice in behavioral interventional trials.

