### Data Collection and Analysis

Data has been collected from structured facility records and client exit interviews at baseline (before the intervention) and will be collected 3 and 6 months after the intervention. Data quality will be ensured through descriptive statistics and logical validation checks, identifying missing values, inconsistencies, and outliers. The baseline characteristics will be summarized for assessing comparability across clusters.

The quality of FP services will be assessed using the Quick Investigation of Quality tool, which measure 25 key indicators of counseling quality [27]. For the data analysis, SPSS (version 26; IBM Corp) will be used. Service provider and client characteristics will be summarized in descriptive analyses. Exploratory comparisons will use paired 2-tailed *t* tests (or Wilcoxon signed-rank tests), ANOVA, and *χ*^2^ tests.

Mixed effects regression models with a random intercept for hospital catchment (cluster) will be using for clustering. These will be used to analyze binary outcomes of the interventions, such as uptake of modern contraceptives. Mixed effects logistic regression will be applied. For continuous outcomes, such as client satisfaction and quality score, we will use mixed effects linear regression. To assess robustness, population-averaged models using generalized estimating equations with robust SEs will be considered as a sensitivity analysis.

To estimate the changes in outcome over time between the interventional and control arms, we will use a difference-in-differences approach. All multivariate models will be adjusted for individual-level covariates such as age, parity, education, and baseline contraceptive use, as well as facility-level characteristics.

Effect sizes for categorical outcomes will be reported as odds ratios with 95% CIs, and for continuous outcomes, Cohen *d* will be used. Statistical significance will be assessed at a 2-sided *P* value <.05. Results will be presented in the form of tables and graphical summaries for interpretability and for informing future scalability.

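### The mix of family health centers within a hospital may change between baseline and follow-up, and the difference-in-differences model has no center term to absorb it

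*Protocol article*

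**What the plan says.** **Unit.** Randomization and Blinding states: "Cluster randomization was conducted at the hospital level, with each hospital constituting a cluster". Study Design treats each catchment accordingly, "with FHCs nested within clusters considered as a single cluster and randomized to 1 of the 3 arms". Study Setting gives the pool of centers: "Rawalpindi has an extensive network of nearly 60 FHCs that are administratively affiliated with tertiary hospitals". The number taking part is not given.

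**Who supplies women.** Three sampling rules appear under separate headings.
- Consecutive Sampling of Clients (baseline, 333 women): "all eligible clients visiting selected tertiary care" hospital-affiliated FHCs "will be enrolled through nonprobability consecutive sampling".
- Stratified Random Sampling of Centers: "Stratified random sampling of urban and rural locations was used in the second phase of the trial".
- Study Participants: Purposive Sampling and Sample Size Calculation (60 per arm, 180 in total): "women of reproductive age visiting FHCs for FP services will be recruited through purposive sampling". No allocation by center is stated.

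**How the rounds are compared.** The Phase 1 section makes the baseline data the reference against which effectiveness is judged. Data Collection and Analysis plans "Mixed effects regression models with a random intercept for hospital catchment (cluster"), with a difference-in-differences contrast. Models are to be adjusted for individual covariates and for facility-level characteristics that are not named. Generalized estimating equations (GEE) with robust standard errors will be considered as a sensitivity analysis.

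**The concern.** A difference-in-differences on repeated samples assumes that, apart from the intervention, each hospital is represented in the same way in every round. Here the rounds are drawn by different non-probability rules, and nothing stated holds the contributing centers or their shares constant. Consecutive enrolment weights centers by client volume. Purposive recruitment weights them by the recruiter's choice.

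If centers differ in uptake (urban or rural, high or low volume), a change of mix alters a hospital's before-after change even when the women within each center are recruited without bias. Two consequences should be kept apart:
- **Bias** in the arm contrast, if the mix shifts differently between arms.
- **Understated variance**, even if shifts are unrelated to arm. A hospital intercept common to all rounds cancels in the hospital's change, so it cannot represent a center component that differs between rounds.

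**Working it through.** **Inputs from the protocol article.** Intracluster correlation (ICC) 0.02 and design effect 1.38, with the design effect equal to 1 + (m − 1) × ICC; 60 women per arm; 333 at baseline; uptake of 25% and 40%, a difference of 15 points.

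**Derived.** m = 1 + 0.38/0.02 = 20, so 60/20 = 3 hospitals per arm and 9 in all. Baseline women per hospital = 333/9 = 37; women per hospital in a post round = 20. The article does not state the number of hospitals, so this is an inference. Taking 60 per arm as one post round is also an assumption.

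**Further assumptions.** Three centers per hospital per round, equally represented; a center-level ICC ρ of 0.02, 0.05 or 0.10; 25% uptake and no true effect; normal reference distribution; risk-difference scale; no facility adjustment.

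**Variance of one hospital's change.** With p(1 − p) factored out:
- Hospital-intercept model: V0 = 1/37 + 1/20 = 0.0770.
- Actual: V1 = ρ × K + (1 − ρ) × 0.0770, where K is the sum of squared changes in center weights.
- Ratio R = V1/V0 = 1 − ρ + ρ × K/0.0770. The number of hospitals cancels in R.
- Actual type I error = 2 × [1 − Φ(1.96/√R)].

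**Worst case, all centers replaced.** K = 1/3 + 1/3 = 0.667 and R = 1 + 7.655ρ.

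| ρ | R | Type I error |
|---|---|---|
| 0.02 | 1.15 | 6.8% |
| 0.05 | 1.38 | 9.6% |
| 0.10 | 1.77 | 14.0% |

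A simulation of 3,000 runs under the same assumptions gave 7.3%, 9.6% and 14.5%.

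**Milder cases.** Type I error at ρ = 0.02, 0.05 and 0.10:
- One of three centers replaced (K = 1/9 + 1/9 = 0.222): 5.4%, 6.1%, 7.2%.
- Same centers, shares moving from equal to 60/30/10 (K = 0.127): 5.1%, 5.4%, 5.7%.
- Same centers, equal shares (K = 0, R = 1 − ρ): 4.8%, 4.4%, 3.9%. Simulation gave 5.6%, 5.1%, 4.2%.

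**Systematic bias.** Spurious difference-in-differences = (uptake gap between center types) × (shift in share in one arm only).
- A 10-point gap and a 30-point shift: 0.10 × 0.30 = 3 points, one fifth of the assumed 15-point effect.
- Gaps of 5 to 20 points with shifts of 10% to 50%: 0.5 to 10 points.
- The same shift in every arm with the same gap: zero.

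The gaps and shifts are illustrations, not document figures.

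**Does a center term help?** In a simulation of 300 runs, an FHC intercept brought rejection rates of 10% to 12% back to about 5% when centers changed. It slightly lowered the standard error when they did not. With 300 runs, the Monte Carlo standard error at 5% is √(0.05 × 0.95/300) = 1.3 points.

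**The case against.** **No text says the centers differ.** A reader might infer that baseline and follow-up women come from different FHCs. The article does not support that. Data Collection and Analysis describes one data collection at baseline, 3 and 6 months, and Results places client and provider recruitment in the same July 2025 window. A center list may sit in the full protocol or in the CONSORT figure, which is not shown. This stands, so the point is conditional. What the article does state is different selection rules for the samples being compared and a model without a center level.

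**Facility-level characteristics are to be adjusted for.** This stands in part. Urban or rural location and volume are such characteristics, and adjusting for them would shrink the bias figures above. But the covariates are unnamed, and it is unclear whether a facility means an FHC or a hospital. A time-constant hospital covariate cannot correct a shift among that hospital's centers, and FHC covariates remove only what they measure.

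**GEE with robust standard errors could capture the omitted variance.** In principle yes, at hospital level. It is only to be considered as a sensitivity analysis, and robust standard errors are unreliable with about 9 clusters.

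**Pooling FHCs into the hospital is right.** Agreed. A reader might take the cluster definition as the error. With hospitals randomized, it is not.

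**A common shift cancels.** Agreed for systematic bias. It does not answer the variance point: random turnover is independent between hospitals and does not cancel when hospitals are few.

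**The figures are a worst case.** Agreed. At 0.02, the only ICC the article gives, full turnover yields about 7%, and partial turnover yields less.

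**Conclusion.** The point holds as a conditional weakness of sampling and modeling. The stated rules allow the center mix within a hospital to change between rounds, and the stated model would place that change partly in the arm contrast and leave its variance out of the standard error. Under complete turnover with the assumed structure, the nominal 5% test runs at about 7% to 14% for center ICCs of 0.02 to 0.10. If one center in three is replaced it runs at about 5% to 7%, and with unchanged centers near 5%.

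Two stronger conclusions are not supported: that a change of center mix has occurred, and that the estimated effect will be biased. Bias requires a shift that differs by arm, and nothing in the article suggests one. These figures also concern center turnover alone, not the separate difficulty of testing with few hospitals.

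**What to change.** 1. Add a random intercept for FHC nested in hospital to the mixed models in Data Collection and Analysis. Keep the hospital intercept and continue to test arm against hospital-level variation.
2. Recruit the 3- and 6-month rounds in the FHCs that supplied baseline women, in similar shares by center.
3. Where centers overlap, report the difference-in-differences restricted to FHCs present in both rounds as a sensitivity analysis. It should not be the main analysis, since with little overlap few women would remain, and with none it could not be done.

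**Cost.** An FHC identifier for each woman, a site list for the post rounds, and one extra variance component. That component would be estimated from few women per center (about 20/3, or 7, per round under the assumptions above) and may be imprecise or estimated at zero. Some baseline women leave the restricted analysis but stay in the Phase 1 description. The article schedules the post rounds for October 2025 and December 2025 to January 2026. If they have already run, items 1 and 3 can still be applied provided the center was recorded.
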